## Abstract

**Background:**

Bacillus Calmette-Guérin (BCG) vaccination may have nonspecific effects, i.e., effects on childhood morbidity and mortality that go beyond its effect on the risk of childhood tuberculosis (TB). Though the available scientific literature is mostly from observational studies, and is fraught with controversy, BCG vaccination at birth may protect infants in high-mortality populations against serious infections other than TB. Yet, other studies indicate that giving BCG later in infancy may modify immune responses to non-TB antigens and potentially enhance immunity, potentially also against tuberculosis (TB). It is unclear whether BCG vaccination very early in life offers adequate protection against TB and other infections among HIV-1-exposed children because even those who remain uninfected with HIV-1 show signs of impaired immunocompetence early in infancy. This study will compare BCG vaccination at birth with BCG vaccination at 14 weeks of age in HIV-1-exposed infants.

**Methods:**

This is an individually randomized controlled trial in 2200 HIV-1-exposed infants. The intervention is BCG vaccination within 24 h of birth while the comparator is BCG given at 14 weeks of age. The study co-primary outcomes are severe illness in the first 14 weeks of life, and production of tumor necrosis factor, interleukin (IL)-1β, IL-6 and interferon-γ in response to mycobacterial and nonmycobacterial antigens. The study is being conducted in three health centers in Uganda.

**Discussion:**

A well-timed BCG vaccination could have important nonspecific effects in HIV-1-exposed infants. This trial could inform the development of appropriate timing of BCG vaccination for HIV-1-exposed infants.

**Trial registration:**

ClinicalTrials.gov, identifier: NCT02606526. Registered on 12 November 2015.

**Electronic supplementary material:**

The online version of this article (doi:10.1186/s13063-017-1881-z) contains supplementary material, which is available to authorized users.

## Background

### BCG vaccination and nonspecific effects

Several observational studies suggest that routine childhood vaccines may have effects on childhood morbidity and mortality that are separate from their effects on the incidence of the diseases that they target [1–6]. Importantly, the Bacillus Calmette-Guérin (BCG) vaccine may have effects on morbidity and mortality that cannot be attributed to the vaccine’s protective effect against tuberculosis (TB) [7–11]. A case control study among infants in Guinea-Bissau showed that infants who had received the BCG vaccine were at least 60% less likely to have acute lower respiratory tract infections (ALRI) and respiratory syncytial virus infections [12] than those who had not been vaccinated. A small Malawian study indicated that the likelihood of septicemia among infants with a BCG scar was lower than that among infants without a scar [13]. A Senegalese prospective study analyzing data from two birth cohorts (a total of 11,369 children under 2 years of age) found an association between a combination of BCG/DTP administered simultaneously and reduced mortality [1]. A secondary analysis of data from a randomized controlled trial among low-birth-weight preterm infants indicated that there may be an association between early BCG vaccination and lower perinatal mortality, but not lower infant mortality [9]. In a birth cohort study in Uganda, we previously showed that children between 1 month and 5 years of age who had received BCG had a substantially lower mortality than those who had not [14]. In fact, this association was even stronger in the neonates but we decided not to display this potentially important finding because of the possibility that some of the association could have been due to reverse causality, as vaccinators could to some extent have refrained from giving BCG to sick babies. Other observational studies among older children, adolescents and adults have shown mixed results for the effects of the BCG vaccine against atopy [15–18] and helminthic infections [19–21]. Nonspecific effects of vaccines, are now receiving increased attention, all the more so when the incidence of the TB is decreasing worldwide [22]. In fact, the World Health Organization (WHO) recently established a Strategic Advisory Group of Experts working group on NSEs of vaccines [23].

### Methodological challenges in existing studies

The medical literature on the NSEs of vaccines is fraught with controversy [7]. Much of this controversy stems from interpretational challenges of the observational studies carried out in high-mortality areas, and in heavily burdened health care systems [24, 25]. It has been argued that children with a lower morbidity and mortality are more likely to be vaccinated than higher-risk children, resulting in a spurious nonspecific protective effect of vaccines in observational studies [24, 25]. There is also the possibility of survival bias if death (a common study outcome) is associated with missing vaccination cards. This has been observed in some retrospective studies in Africa where child deaths were quickly followed by destruction or loss of vaccination cards [1, 24, 26, 27]. These selection challenges can be alleviated by well-designed and well-executed randomized controlled trials. However, as most childhood vaccines are part of routine national and international child health programmes, it has been considered unethical to randomize children to not receive BCG. For this reason, the medical literature on NSEs has continued to be overshadowed by controversy and continues to be dependent on initial studies carried out several decades ago when morbidity and mortality patterns, as well as the vaccines themselves, were different from what they are now [24, 25]. Two recent systematic reviews concluded that the currently available evidence, which is mainly from observational studies, was of low quality and reiterated the need for randomized controlled trials [28, 29]. To the best of our knowledge, there are currently no other, long-term, ongoing randomized trials with clinical endpoints similar to ours.

### Immunological reprogramming induced by BCG

In order to strengthen the medical literature, one of the most important aims of the study is to identify any immunological reprogramming induced by BCG, which has been recently suggested to be responsible for NSEs [30]. The immunological responses thought to account for the NSEs of BCG may, in broad terms, be considered to involve two processes: trained innate immunity and heterologous immunity. Trained immunity is a novel concept that describes the functional reprogramming of innate immune cells (such as monocytes, macrophages or natural killer (NK) cells) after an infection or vaccination [31]. The molecular mechanism mediating trained immunity is represented by epigenetic modifications due to changes in histone methylation and acetylation, leading to a looser chromatin structure and increased gene transcription [32]. Similar epigenetic reprogramming has been described in monocytes of individuals vaccinated with BCG [33]. In addition to trained immunity, a second important immunological mechanism that is likely to be involved in the NSEs is heterologous immunity: the capacity of memory T-lymphocytes to respond in an interleukin (IL)-12/IL-18-dependent manner with increased production of cytokines upon stimulation with different stimuli [34].

### Timing of BCG vaccination among HIV-1-exposed children

Based on studies showing a nearly 1000-fold increased risk of disseminated BCG infection among HIV-1-infected infants, recent WHO guidelines consider HIV-1 infection a contraindication to BCG vaccination [22, 35, 36]. However, the practical implementation of this guideline has been difficult as HIV-1 diagnosis at birth (when the vaccine is to be given) is not available in many low- and middle-income countries (LMICs) [35, 37]. As a result, all HIV-1-exposed infants, including those yet to be diagnosed as HIV-1 infected, continue to receive BCG at birth in several LMICs [35, 37]. To circumvent this, an alternative approach has been proposed in which the vaccine is delayed until these infants are diagnosed as not having HIV-1 infection [35, 37].

On the one hand, if vaccinating HIV-1-exposed babies with BCG at birth protects them against serious infections other than TB, i.e., through NSEs [7, 8, 11], delaying vaccination could result in increased morbidity and even mortality. In addition, delaying BCG vaccination to a later time when a definitive diagnosis is made could reduce its coverage [37]. The Ugandan Ministry of Health has decided that all infants, including those with HIV-1 infection, but without symptomatic HIV-1 disease, are to receive BCG.

On the other hand, recent studies put into question the age at which the BCG vaccine is best given to HIV-1-exposed and uninfected children [35, 38–41]. It is presently unclear whether BCG vaccination very early in life provides them with adequate protection against TB and other infections. HIV-1 infection during pregnancy may transiently modulate their responses to the BCG vaccine [38]. It appears that they have an impaired response to purified protein derivative (PPD) and heat-killed BCG in comparison to unexposed children [38]. These effects seem to be greatest among younger HIV-1-exposed uninfected children. A recent study in Brazil found the cellular immune response to BCG among younger HIV-1-exposed uninfected children to be impaired in comparison to their unexposed counterparts [35]. BCG-specific T-cell proliferation and interferon (IFN)-γ concentrations were lower in the younger than in the older HIV-1-exposed uninfected infants and than in the unexposed infants. This signified a delay in immune system maturation of HIV-1-exposed infants. Moreover, a Gambian study showed that children vaccinated at a median age of 14 days were less likely to develop a BCG scar if they were HIV-1-exposed uninfected than if they were HIV-1-unexposed and uninfected [39]. A Rwandese study did not replicate this finding but found that HIV-1-exposed uninfected children vaccinated at birth were substantially less likely than HIV-1-unexposed children to react to a tuberculin skin test at 6 months of age [40]. Other studies have linked negative tuberculin skin tests and absence of BCG scars to high morbidity and mortality in children [41]. These BCG-specific immune abnormalities are consistent with a wider range of other anomalies reported among very young HIV-1-exposed uninfected children and are thought to result from in-utero exposure to the HIV-1 infection and/or antiretroviral drugs. These include: a reduced CD4/CD8 ratio, reduced CD4+ and CD8+ naive T-cell percentages, an increased percentage of activated CD8+ T-cells, augmented percentages of CD3(+)/4(−)/8 (−) (DN) and DN/25(−)/44 (+) [42–44], altered cell-mediated immunity and T-cell maturation [42], reduced IL-12 production that persists until 6 months of age that could possibly be immunosuppressive [45], and several cytokine and other immune abnormalities [42, 43, 45–47]. Importantly, many of these anomalies appear to be transient, disappearing as children grow older.

A small trial in South Africa in which newborn HIV-1-unexposed babies were randomized to receive BCG at birth or at 10 weeks of age, showed that delaying the vaccination resulted in increased numbers of BCG-specific CD4 T-cells, most importantly polyfunctional T-cells co-expressing IFN-γ, tumor necrosis factor (TNF)-α and IL-2, at 1 year of age [48]. A recent study among HIV-1-exposed children reported robust T-cellular responses to *Bordetella pertussis* and tetanus toxoid in infants in whom BCG vaccination was delayed to 8 weeks of age [49]. It is unknown, whether these effects of delayed BCG administration translate into enhanced protection against TB or, for that matter, against other serious infections.

The most appropriate timing for BCG vaccination that maximizes both specific and possible NSEs, particularly in HIV-1-exposed children, is thus presently unknown. This uncertainty compels us to study the NSEs of the BCG vaccine with a design that overcomes the methodological challenges of observational studies.

### Purpose and rationale of this study

A rapid increase in the number of HIV-1-positive pregnant women receiving antiretroviral treatment (ART) to prevent mother-to-child transmission (MTCT) of HIV-1 in the last 10 years [50], coupled with stagnating or increasing adult HIV-1 prevalence in LMICs, has resulted in an increase in the number of HIV-1-exposed uninfected children [51–53]. While data on HIV-1-exposed uninfected children is scanty, available evidence suggests that these children have a higher morbidity and mortality in comparison to their unexposed counterparts [54, 55]. In comparison to unexposed children, HIV-1-exposed uninfected children are more likely to contract the common childhood infectious diseases in severe forms [56–58], more likely to be hospitalized and more likely to be resistant to treatment [59–62]. They are also vulnerable to diseases previously reported among immunocompromised children, such as cytomegalovirus colitis [63], hemorrhagic chicken pox, *Pneumocystis jiroveci* pneumonia and others [64].

Bearing the above considerations in mind, we believe that there is clinical equipoise between early and deferred BCG vaccination in HIV-1-exposed, and probably even in HIV-1-unexposed infants. Moreover, the long-term cost-implications and cost-effectiveness of the alternatives have never been investigated.

It is possible that well-timed BCG vaccination could have important NSEs in HIV-1-exposed children. We therefore propose a parallel-group superiority trial that could inform the development of programmatically appropriate timing of BCG vaccination for HIV-1-exposed infants by measuring the safety, potential benefits or disadvantages, costs and cost-effectiveness of early versus late BCG.

## Methods/design

### Hypotheses

Compared to deferring BCG vaccination until 14 weeks of age, BCG administered within the first 24 h of birth leads to at least a 30% relative risk reduction of severe illness^1^ among HIV-1-exposed infantsDelayed BCG results in at least a 30% higher production of TNF, IL-1β, IL-6, IL-10, IL-17, IL-22 and IFN-γ in response to mycobacterial (from *Mycobacterium tuberculosis* and PPD) and non-mycobacterial (from *Escherichia coli, Candida albicans* and *Staphylococcus aureus*) antigens compared to when BCG is administered at birth in HIV-1-exposed infants

### Primary objectives

To compareThe risk of severe illness in the first 14 weeks of life, andThe production of TNF, IL-1β, IL-6, IL-10, IL-17, IL-22 and IFN-γ in response to mycobacterial (from *M. tuberculosis* and PPD) and non-mycobacterial (from *E. coli, C. albicans and S. aureus*) antigens at birth (before BCG vaccination) and at 1, 14, 15 and 28 weeks of age among HIV-1-exposed infants administered BCG at birth with those administered a delayed BCG

### Secondary objectives

To compare:The risk of severe illness from 48 h after randomization until 14 weeks of life among HIV-1-exposed infants administered BCG at birth with those receiving delayed BCGHIV-1-exposed infants who received BCG at birth with those administered a delayed BCG with respect to the occurrence of diarrhea, pneumonia and/or severe illness from 14 weeks to 1 year of ageHIV-1-exposed infants who received BCG at birth with those administered a delayed BCG with respect to the occurrence of severe illness during infancyOccurrence of diarrhea, pneumonia and/or severe illness during infancy in HIV-1-exposed infants vaccinated with BCG at birth versus those who receive delayed BCGThe mortality from birth to 14 weeks of age in HIV-1-exposed infants vaccinated with BCG at birth versus in those who are yet to receive BCGInfant mortality between HIV-1-exposed babies vaccinated with BCG at birth versus in those who receive delayed BCGThrough life-cycle modeling, long-term aggregate health benefits and cost-implications of the delivery strategies, and estimate their cost-effectiveness

To increase the diagnostic specificity, we will also try to capture “clinical sepsis^2^,” where an infant with severe illness and a negative blood culture, or from whom a blood culture could not be taken, has two or more of the following findings: total lymphocyte count (TLC) <5000 cells/mm^3^, absolute neutrophil count <1,500 cells/mm^3^, band to total polymorph ratio >0.2 and both of two C-reactive protein (CRP) levels >1 mg/dl in two specimens taken 24 to 48 h apart. Because we are yet to know in what proportion we can manage to collect the required blood specimens, the comparison between the risk of “clinical sepsis” and/or “confirmed sepsis^3^” between the two trial arms will form part of our secondary analyses. Although it is unclear whether BCG scarring is a marker of immune responsiveness in general and it may be that such scarring is unrelated to protection against TB, it is being captured as a marker of “vaccine take.” We will also explore whether children with a scar are less or more prone to severe illness during infancy. The study will also examine the effect of the timing of BCG administration on infant growth.

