Upon enrollment and on subsequent visits, mothers and other caregivers are informed about symptoms and signs of severe illness, and are encouraged to contact the study clinic in case the baby develops any of these symptoms. Each mother is provided with a durable note book, in which she is instructed and trained to note down all relevant events in her child. The front page of the book will have clear reminders that she needs to contact the study team in case the child visits a health clinic, a physician or is admitted to a hospital. A child who comes to a clinic with such symptoms is examined by a study nurse/midwife. If the child does not attend after the mother/caregiver has informed the study team of such signs or for a scheduled visit, the study nurse/midwife will make a visit to the child’s house. If the nurse/midwife classifies the condition as possible severe illness, a study physician will be called to examine the child. If the physician classifies the child as having severe illness, they will collect a blood specimen for blood culture (using BACTEC) and a sepsis screen (CRP, TLC, differential count, and band cell:neutrophil count ratio) as soon as possible. A repeat specimen will be collected again for CRP between 24 and 48 h. The study team will do its utmost to obtain specimens for such a sepsis screen from as many infants with signs of severe illness as possible. However, we have yet to learn what percentage of them in this way can actually be screened for “clinical sepsis.” When 200 enrolled babies have been followed until the age of 6 months, the percentage of infants registered as having had severe illness who are screened for clinical sepsis will be calculated. If this percentage is less than 80%, measures will be taken to increase it above this value, if these measures are unsuccessful, we will need to abandon the attempt to identify clinical sepsis with the sepsis screen. Length and weight measurements are taken twice at each visit, based on the WHO guidelines, and z-scores calculated using WHO child growth standards [68].

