## Clinical laboratory tests

Heel-prick blood samples are obtained from the children for HIV-1 diagnosis. Dried blood spots (DBS) using a commercial PCR kit are used for HIV-1 diagnosis. This testing is supported by standardized protocols that have been successfully validated in Uganda. Flow cytometry is used for CD4 count measurement while standardized automated procedures and techniques are used for hematological and biochemical plasma assays. ELISA and/or rapid tests are used for maternal HIV-1 diagnosis according to the Ugandan national guidelines. At week 14 and week 52, blood will be drawn by venipuncture for full/complete blood counts. TLC, differential count and CRP will be captured as part of the sepsis screen in babies with clinical severe illness.

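### One of the four clinical sepsis findings is written as a lymphocyte count below 5000, but the listed sepsis screen fits a total leukocyte count better; the analyte should be confirmed before cases are classified

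*Protocol article*

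**What the plan says.** All references are to the protocol article.

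- **Secondary objectives.** Clinical sepsis applies to an infant with severe illness whose blood culture is negative or could not be taken, and who "has two or more of the following findings". The four findings are "total lymphocyte count (TLC) <5000 cells/mm" (cubed), "absolute neutrophil count <1,500 cells/mm" (cubed), "band to total polymorph ratio >0.2", and two CRP values above 1 mg/dl in specimens 24 to 48 hours apart. The purpose is given at the start: "To increase the diagnostic specificity, we will also try to capture" this outcome.
- **Follow-up and subject retention.** The physician takes a blood culture and "sepsis screen (CRP, TLC, differential count, and band cell:neutrophil count ratio").
- **Clinical laboratory tests.** The second listing is shorter: "TLC, differential count and CRP will be captured as part of the sepsis screen".
- **Abbreviations.** TLC does not appear, so Secondary objectives holds its only expansion.
- **Secondary analysis.** The risk of clinical sepsis is to be analysed for the first 14 weeks and for the remaining 38 weeks of infancy.

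**The concern.** The definition puts the 5000 cut-off on lymphocytes, while the two lists of tests read more naturally if TLC is the total leukocyte count. An absolute neutrophil count is normally total leukocytes times the neutrophil share from the differential, and a lymphocyte count listed next to a differential adds little that the differential does not already carry.

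The choice decides who is a case. Someone coding from Secondary objectives would test lymphocytes. Someone coding from the laboratory's TLC field might test leukocytes. The two could classify different infants as septic. The literal reading is the looser one, and it sits inside a rule that needs only two findings out of four, so it works against the stated aim of specificity. If the extra cases are illnesses on which BCG timing has little effect, they dilute the between-arm contrast for this outcome.

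**Working it through.** The document gives no event rate, sample size or power for clinical sepsis, so there is no stated figure to reproduce. The check has three steps.

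**1. Direction, by logic alone.** Lymphocytes cannot exceed leukocytes. Leukocytes below 5000 therefore imply lymphocytes below 5000, but not the reverse. Example: 8000 leukocytes with 50% lymphocytes gives 8000 x 0.5 = 4000 lymphocytes. This infant meets the criterion as written and would not meet a leukocyte criterion.

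**2. Which reading fits the listed screen.**
- If TLC is leukocytes and the differential is in percentages, the neutrophil count takes one step: 8000 x 0.4 = 3200.
- If TLC is lymphocytes, it can still be back-calculated as lymphocytes / lymphocyte share x neutrophil share: 4000 / 0.5 x 0.4 = 3200.
- If the differential is in absolute counts, the neutrophil count is read off directly under either meaning.

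The list therefore favours leukocytes without excluding lymphocytes.

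**3. Illustration of size. Every rate here is an assumption.** Among severely ill infants without sepsis, let q be the chance of meeting the count criterion and p the chance of meeting each of the other three, all independent. The false-positive share is

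fp = q[1 - (1 - p)^3] + (1 - q)[3p^2(1 - p) + p^3].

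Take q = 0.05 for the narrower leukocyte criterion, q = 0.30 to 0.70 for the wider lymphocyte criterion, and p = 0.05 to 0.15. Per unit of severe illness in the delayed arm, let true sepsis be 0.20, with a true risk ratio of 0.70 (so 0.14 in the birth arm), sensitivity 0.8, and non-septic illness 0.80 in both arms. Then

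observed RR = (0.14 x 0.8 + 0.80 fp) / (0.20 x 0.8 + 0.80 fp).

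| p | q | fp | observed RR |
|---|---|---|---|
| 0.05 | 0.05 | 0.014 | 0.72 |
| 0.05 | 0.30 | 0.048 | 0.76 |
| 0.05 | 0.70 | 0.102 | 0.80 |
| 0.10 | 0.05 | 0.040 | 0.75 |
| 0.10 | 0.30 | 0.101 | 0.80 |
| 0.10 | 0.70 | 0.198 | 0.85 |
| 0.15 | 0.05 | 0.077 | 0.78 |
| 0.15 | 0.30 | 0.158 | 0.83 |
| 0.15 | 0.70 | 0.288 | 0.88 |

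First and last rows in full: (0.112 + 0.0112) / (0.16 + 0.0112) = 0.72, and (0.112 + 0.2304) / (0.16 + 0.2304) = 0.88. The range is 0.72-0.78 for the narrow criterion and 0.76-0.88 for the wide one. The ranges overlap across values of p, but at any one p the wider criterion always lies nearer 1.

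**Sensitivity to the key assumption.** Suppose non-septic severe illness also falls by 30% in the birth arm, to 0.80 x 0.70 = 0.56. Then RR = (0.112 + 0.56 fp) / (0.16 + 0.80 fp) = 0.70 for every fp, and there is no dilution.

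**The case against.** **No passage contradicts another outright.** TLC is expanded once, and the two lists use only the abbreviation, so the mismatch is inferred. This stands: the document suggests a slip and does not prove one. The note attached to the term clinical sepsis is not in the text at hand, and neither is the laboratory procedure. Either may already settle the point.

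**A reader might infer that the neutrophil criterion cannot be computed unless a total leukocyte count is added to the screen.** The document does not support that. As shown in the working, the count can be back-calculated, or read directly from an absolute differential.

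**A reader might infer that the literal wording defeats the purpose of the definition or necessarily biases the risk ratio.** Neither follows. Clinical sepsis requires severe illness plus two findings, so it is a subset of severe illness and cannot be less specific than severe illness under either reading; only the gain can shrink. Movement toward 1 needs BCG timing to affect non-septic severe illness less than sepsis, whereas Hypothesis A posits a reduction of at least 30% in severe illness as a whole.

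**The consequence is limited.** Clinical sepsis is absent from the list of secondary outcome measures, and Follow-up and subject retention allows the attempt to be abandoned if screening stays below 80% of severe illnesses. This bears on weight, not on correctness: the comparison is still planned under Secondary analysis, and the article itself states the analyte, cut-off and rule.

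**Conclusion.** The point holds as a case-definition ambiguity with a known direction and an unknown size. The only expansion of TLC puts the cut-off on lymphocytes, and the listed screen fits leukocytes better. Applied literally, the criterion admits at least as many infants as a leukocyte criterion at 5000, so more severely ill infants without sepsis may be labelled as cases.

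The document gives no distribution of lymphocyte or leukocyte counts in ill infants, so the effect on the result cannot be derived from it. The shift from 0.72-0.78 to 0.76-0.88 for a true risk ratio of 0.70 illustrates the mechanism. It rests on assumed positivity rates, independence of the criteria, 80% sensitivity, a 20% sepsis share of severe illness in the delayed arm, and no effect of BCG timing on non-septic illness. Only this secondary analysis is affected; the primary outcomes and the sample size are not. The correction is worth making because it is cheap and can change who counts as a case.

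**What to change.** Before analysis, check the definition under Secondary objectives against the laboratory procedure and state which count TLC denotes.

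- If it is the total leukocyte count, replace lymphocyte by leukocyte in the definition and make sure the case-definition code uses that variable.
- If lymphocytes are meant, justify the 5000 cut-off and state how the absolute neutrophil count is obtained from the screen.

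In either case, use the same term under Follow-up and subject retention and under Clinical laboratory tests, and add TLC to the abbreviations. The cost is a one-word correction or a short justification, plus a check of the code. No further specimens or tests are needed.
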